**Methods/design:**

A two-arm cluster randomized controlled trial employing a wait-list control plus qualitative and mixed-method evaluations was used. Participants were school pupils from Years 7 and 8 (aged 11–13 years). Ten schools located in southwest England were randomly allocated to receive the BtBYCB intervention (n = 5 schools; 711 pupils) or a control condition (i.e., usual Personal, Social, and Health Education classes) (n = 5 schools; 622 pupils). Participants in the intervention condition received a program consisting of (i) a talk from an Olympian/Paralympian; (ii) 11 one-hour teacher-led PSHE classroom sessions in which pupils identified their aspirations, values, and interests and explored and acted on these via activities such as personal development planning, goal-setting, and peer-mentoring; and (iii) participated in a celebration event (e.g., second visit from Olympian/Paralympian and short individual presentations). Data were collected at baseline, post-intervention, and at 3-month follow-up.

Focus groups (pupils and teachers) and individual interviews (headteachers) were conducted in the 5 intervention schools to (i) gain an in-depth understanding of mechanisms of change; (ii) explore ways in which the participants’ motivation and engagement could be enhanced, and (iii) elicit user-feedback pertaining to how the program, content, and appeal could be improved.

A mixed-method approach was used to describe and explain the differing experiences of particular groupings within and across the intervention schools; i.e., those for whom the program was effective, those that experienced little, if any change, and those for whom the program led to an inverse effect.

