### Design

A single center CRCT employing a wait-list control group, supplemented by focus groups and a mixed methods process evaluation. The unit of randomization was school. Individual pupils will be the unit of analyses, yet we will take into account the nesting effects of schools and classes.

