### Participants and setting

Secondary school children aged between 11 and 13 years attending 10 schools in the southwest of England served as participants in this project. Following ethical approval, parental consent, and participant assent, 1333 pupils were recruited for the CRCT using a cluster sampling approach. Pupils were randomly assigned by their school to either (i) BtBYCB intervention (n = 711 pupils from 28 classes) or (ii) a control group receiving standard PSHE lessons (i.e., standard care; n = 622 pupils from 30 classes). For the secondary analyses, a randomly selected sample of pupils and teachers were selected from each of the five intervention schools (n = 5). For the mixed-methods element, participants in each of the five schools were stratified by outcomes using a tertile split so as to acquire a purposeful sample encompassing different pupil experiences of the BtBYCB intervention (8 participants per grouping in each of the 5 intervention schools).

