### Sampling and randomization

To reduce contamination effects and bias, school was used as the randomization unit in this work. Allocation to either the intervention or the control arms of the trial occurred after schools had been recruited. A block randomization (1:1 ratio) was performed by an independent agency (i.e., in this case a trained individual within the SouthWest Regional Development Agency) and the balance between the trial arms was based on the following strata: socioeconomic status, urban/rural, and small/large. In agreeing to partake in this work, the school’s senior management had to be willing to accept the randomization status of the school. Potential disappointment with being allocated to the control condition was offset by the use of a wait-list control.

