### Sample size calculation

Using a sample size calculator software package [21], the 58 classes used in this work based on the average size of class (i.e., 25 pupils; [22]) permitted the detection, at the 5% significance and 90% power level, of a standard difference of 0.25 (i.e., .25 of a standard deviation can be detected with an intra-cluster correlation (ICC) of .05). In recognizing that some classes were smaller than the average 25 pupils, a more conservative estimate using the same criteria (5% significance with 90% power assuming an ICC of .05) showed that .27 of a standard deviation could be detected with 50 classes with 25 pupils in each cluster. The current sample size also accommodates analyses at school and classroom levels (i.e., pupils are nested within classes which are, in turn, nested within schools).

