### Data Analyses

Initially, analysis of variance (ANOVA) will be conducted to establish significant differences for the primary and secondary outcome variables between the two trial arms (allowing for the effects of nesting). Effect sizes, confidence intervals and confidence levels will be calculated. Changes from baseline in the primary and secondary end-points will be analyzed using an analysis of covariance (ANCOVA) model with the intervention as the main factor and baseline as a covariate. Further, multilevel modeling (using HLM 7 software; [47]) will be used to assess the strength of the effect of the intervention on the outcome variables (both primary and secondary) when controlling for nesting effects. Class and school will represent higher order units of analysis, and individual responses the lower order unit of analysis. In such analyses, it is possible to enter class and/or school as a random effect and all other variables as fixed effects.

For the focus groups and individual interviews, the recordings will be transcribed verbatim and analyzed using interpretive phenomenological analysis [48]. Statements will be coded by the investigators and a research assistant with themes within and across participants being extracted. Dependability and trustworthiness of the analysis will be demonstrated through; (i) researcher triangulation (i.e., discussion between researchers to establish all inferences are supported by the data), (ii) the triangulation of qualitative with quantitative data [49], and (iii) participant debriefing to check the researcher’s interpretations, and allow interviewees to make further comments.

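### The sentence that specifies the random effects makes school optional, so a class-only model that omits the randomised unit would comply with the protocol

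*Protocol article*

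**What the plan says.** All references are to the protocol article.

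- **Allocation.** Under Design: "The unit of randomization was school". Sampling and randomization repeats it: "school was used as the randomization unit in this work". The abstract gives ten schools, five per arm. Participants and setting gives "BtBYCB intervention (n = 711 pupils from 28 classes") and "standard care; n = 622 pupils from 30 classes".
- **Intention.** Design says that pupils are the unit of analysis and that nesting in schools and in classes will be allowed for. Data Analyses names class and school together as the higher-order units of the multilevel model.
- **Random effects.** The next sentence of Data Analyses is the only one that specifies them: "In such analyses, it is possible to enter class and/or school as a random effect and all other variables as fixed effects".
- **Sample size.** With 58 classes of 25, the design "permitted the detection, at the 5% significance and 90% power level, of a standard difference of 0.25", at an ICC of 0.05. The only cluster level in that calculation is class. The section closes by saying that the sample also accommodates analyses at school and classroom levels.

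**The concern.** The intervention is a school-level variable, so its effect is estimated by comparing five schools with five schools. Variation between schools enters that comparison in full, and a valid standard error has to include it. A model with class as the only random effect treats 58 classes as if each had been allocated independently. If schools differ at all, its standard error is too small.

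Read literally, the random-effects sentence admits three models: class only, school only, or class within school. The class-only version is the harmful one. The sentence makes everything else a fixed effect, but entering school as a fixed effect would not rescue that model, because allocation is completely confounded with school.

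The multilevel model is to be applied to both primary and secondary outcomes, so the choice affects the intervention test for all of them. Leaving it open also means that the random structure could be settled after the results are seen.

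**Working it through.** **1. Reproduce the plan's own figure, to see which cluster level it uses.** Inputs from Sample size calculation: 5% significance (sidedness not stated; two-sided assumed), 90% power, ICC 0.05, 25 pupils per class.

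- Design effect = 1 + (25 − 1) × 0.05 = 2.2.
- 58 classes: effective n per arm = 29 × 25 / 2.2 = 329.5. Detectable difference = (1.960 + 1.282) × √(2/329.5) = 0.2525 SD, against 0.25 stated.
- 50 classes: effective n per arm = 25 × 25 / 2.2 = 284.1. Detectable difference = 0.272 SD, against 0.27 stated.

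Both figures reproduce with class as the cluster and no school term.

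**2. Standard error with and without school.** Write s for the school share of variance and c for the further class share, with s + c = 0.05. Treating the article's 0.05 as the total same-class correlation is an assumption, and so is its split, because no school-level ICC is given. Take 29 classes per arm, 5.8 classes per school (58/10) and m = 1333/58 = 22.98 pupils per class.

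- True variance of an arm mean: V_true = s/5 + c/29 + (1 − s − c)/(29m).
- Variance that a class-only analysis works from: V_model = S²/29, where S² = c + (1 − s − c)/m + s × (29 − 5.8)/28.
- Understatement of the standard error: r = √(V_true / V_model). Approximate type I error = 2[1 − Φ(1.96/r)].

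Worked at s = 0.01, c = 0.04:

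- V_true = 0.002000 + 0.001379 + 0.001425 = 0.00480.
- S² = 0.0400 + 0.0413 + 0.0083 = 0.0896, so V_model = 0.00309.
- r = 1.25, giving a type I error of about 11.6%.

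**3. Simulation check.** 40,000 null trials per row, with 28 and 30 classes in 5 + 5 schools. The classes per school are assumed to be as even as possible. A t test on class means (56 df) stands for the class-only model, and a t test on school means (8 df) for the school-level analysis. There is no covariate adjustment.

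| School ICC s | Class share c | r | Type I error, class only | Type I error, school level |
|---|---|---|---|---|
| 0 | 0.05 | 1.00 | 5.1% | 5.0% |
| 0.005 | 0.045 | 1.13 | 8.1% | 5.0% |
| 0.01 | 0.04 | 1.25 | 11.2% | 5.0% |
| 0.02 | 0.03 | 1.46 | 17.7% | 5.1% |
| 0.03 | 0.02 | 1.65 | 23.1% | 4.9% |
| 0.05 | 0 | 2.00 | 32.7% | 5.1% |

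If school variance is instead added on top of a class share of 0.05, the class-only rates are 10.7%, 15.4% and 24.4% at s = 0.01, 0.02 and 0.05.

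A smaller run (451 to 600 trials per scenario) that fitted a class-only random-intercept model by REML gave 5.7%, 19.3% and 37.3% at s = 0, 0.02 and 0.05. The last had frequent convergence warnings. It supports the direction and order of size, no more.

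**The case against.** The best defence is that the article commits to both levels elsewhere. Design says that nesting in schools and classes will be allowed for, and the sentence just before the one at issue names both as higher-order units. The sample size section describes pupils within classes within schools. The random-effects sentence can then be read as a remark on what multilevel models can do. A reader might infer from *and/or* that the trial will ignore school; the documents do not support that, and no passage says so. What remains is that the only sentence about random effects makes each level optional, and nothing makes school mandatory.

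A second defence is that the size is conditional. This stands. A reader might infer that the false-positive rate is well above 5% as a matter of fact. The documents give no school-level ICC, there is no inflation at zero, and it is modest at 0.005. The 33% figure requires that classes within a school do not differ at all beyond sampling of pupils. Allocation was balanced on socioeconomic status, urban/rural setting and size, and the analysis is to adjust for baseline and for variables such as SES and ethnicity. These may reduce residual differences between schools. The table should be read at the residual school ICC, which is unknown.

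A third defence is that degrees of freedom belong in an analysis plan that is not shown. That also stands. The article names no reference distribution, so it cannot be faulted for using a normal one. Degrees of freedom appear below only as part of a complete fix.

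**Conclusion.** The point holds as a permissive specification that conflicts with the article's own stated intention. Someone who fitted class as the sole random effect would be following the random-effects sentence and matching the power calculation, and would have left out the randomised unit.

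The cost of that choice, at a nominal 5% level, runs from none at school ICC 0, through about 8% at 0.005, 11% at 0.01 and 18% at 0.02, to 33% at the extreme. This rests on a total same-class correlation of 0.05, an assumed split between school and class, and no covariate adjustment. Analysis at school level holds its level throughout that range, at 4.9% to 5.1% in the table.

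**What to change.** Replace the *and/or* sentence with a requirement along these lines:

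> *School (level 3) and class nested within school (level 2) are both entered as random effects in every primary and secondary outcome model. The intervention effect is tested on school-level degrees of freedom, or with an equivalent small-sample correction.*

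With ten schools and two arms the degrees of freedom are about 10 − 2 = 8, and fewer if school-level covariates are added. This brings the sentence into line with Design and with the sentence before it.

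The edit is one sentence. Its price is wider confidence intervals. With school as the unit on 8 df, 25 pupils per class, the same total correlation of 0.05 and no adjustment, power at 0.25 SD would be about 80%, 62%, 50% and 31% at school ICC 0, 0.01, 0.02 and 0.05, against the stated 90%. That loss comes from randomising ten schools; a class-only model would conceal it.

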## Discussion

Within this paper, a study protocol outlining a robust and systematic empirical assessment of the effectiveness of the BtBYCB intervention on indices of pupil well-being, learning, and health has been described. The protocol described also permits the testing of theoretically-informed mediators designed to form “active ingredients” of the BtBYCB intervention. A strength of framing the work within an empirically supported framework of motivation is that a detailed understanding of how and why the BtBYCB impacts on the primary and secondary outcome variables can be gleaned. That is, the effects of different intervention components can be mapped onto key determinants shown to be robust predictors of high quality forms of motivation as well as indices of adaptive health and well-being [cf. 5,6]. The work is also novel by adding a qualitative and mixed-methods approach to gaining a better understanding of the intervention. That is, the use of the simultaneous mixed-methods approach builds on recent calls for such methods [e.g., 13] and to our knowledge represents the first application of such an approach in the extant SDT-related literature. Such an approach can be readily extended and modified to other areas of study that focus on the mechanisms underpinning adaptive and sustained behavior-change.

There are a number of limitations worthy of note. First, the follow-up period of 3 months is short in duration. Second, many of the measures used were self-report in nature. Thus, issues surrounding common method variance and reporting biases cannot be negated. Future work assessing the BtBYCB program would benefit from using more objective measures across all participants (i.e., we assessed physical activity via accelerometry, but only within a subsample of participants). Future evaluation should also include cost-effectiveness analyses to ascertain whether the intervention leads to meaningful changes within a financially sustainable model.

Findings from this work will be disseminated to practice based audiences (e.g., workshops, practitioner/professional journals, presentations to school-bodies and/or public health departments), lay summaries of findings to the general media (e.g., via newspapers, radio, the internet, and television), and within peer-review articles and conference presentations. The results from this research will be reported akin with the Consolidated Standards of Reporting Trials (CONSORT) recommendations [50].

## Abbreviations

BMI: Body Mass Index; BtBYCB: Be the best you can be program; CRCT: Cluster randomized controlled trial; PSHE: Personal social and health education classes; SDT: Self-determination theory.

